### Recruitment

5.7

Patients managed with internal and external fixation for femoral shaft fracture at the study sites will be recruited to participate in the study. The participants will be recruited 2 weeks post-discharge at the follow-up clinic with the orthopaedic surgeon. Consenting participants will be assessed for eligibility and eligible participants will be allocated into the intervention or control group.

### Allocation

5.8

Blocked allocation will be used to allocate the participants into groups. Random numbers will be generated to allocate the patients into intervention and control groups in blocks (10 numbers equally distributed into intervention and control groups). There will be two blocks namely

1.HIV-positive and2.HIV-negative blocks.

The number allocation will be done by independent research support. Opaque envelopes will be used to conceal the allocation.

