**Figure 1 F1:**
[figure not shown]
Modified anticipated CONSORT flow diagram for a single-blind randomised controlled trial of physical exercise intervention for bone health in the patients.

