### Phase two

5.2

The second phase of the study will aim to determine the effects of physical exercises on BMD, immune and inflammatory markers and functional capacity in adults living with HIV in Nigeria and South Africa with femoral shaft fracture.

*Trial design:* The proposed study design is a multi-center parallel group assessor-blinded randomized controlled trial with allocation ratio of 1:1.

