### Eligibility criteria

5.4

The study population will consist of all persons with femoral fracture and HIV-positive and negative (HIV-positive medically confirmed) aged 18 to 60 years attending the above-named health facilities. For the HIV-positive participants, a documented positive HIV result, as well as a history of being followed-up at the HIV treatment and care center.

Inclusion criteria

Only patients between 18 and 60 years at the last birthday and not more than 60 years at the next birthday.For HIV-negative participants, willingness to accept HIV testing.All patients on ART therapy with femoral shaft fracture will be recruited.All patients with lower limb fractures (femur) will be recruited.All patients must be ambulant.

Exclusion criteria

Severely ill persons based on investigator judgment.Presence of any bone or rheumatic disorder.Fracture of the femoral neck.

*Interventions*: The intervention programme will be a home-based exercise programme targeted at improving bone mineral density, function, gait, QoL, and physical activity. The intervention programme aims to improve the joint range of motion, gait training, muscle strengthening, and balance. The participants in the intervention group will be followed up weekly via phone calls to monitor the intervention and ensure adherence to the programme.

*Control group*: The control group will continue with their usual rehabilitation programme as conducted by the various clinics.

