### Blinding

5.9

The assessors and the data analysts will be blinded to the participant's assigned groups.

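### A single, published block size of 10 would let up to one in six allocations be deduced with certainty, if recruiters see earlier allocations in a list kept to their own clinic

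*Protocol article*

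**What the plan says.** The Phase two section (5.2) describes a "multi-center parallel group assessor-blinded randomized controlled trial with allocation ratio of 1:1". Section 5.8 (Allocation) sets the method: random numbers allocate patients "in blocks (10 numbers equally distributed into intervention and control groups", so each block holds 5 intervention and 5 control places. HIV status is the only stratifier named: "There will be two blocks namely" HIV-positive and HIV-negative. An independent research support does the allocation, and "Opaque envelopes will be used to conceal the allocation". No second block size and no withholding of the size is mentioned.

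On masking, section 5.9 says that "The assessors and the data analysts will be blinded to the participant's assigned groups". The caption of Figure 1 calls the study a "single-blind randomised controlled trial of physical exercise intervention". Patients and treating staff are not listed as blinded.

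Recruitment takes place at the orthopaedic follow-up clinic (5.7), where eligibility is assessed before allocation. One exclusion in section 5.4 is discretionary: "Severely ill persons based on investigator judgment". Sampling is consecutive (5.6).

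**The concern.** Concealment has two parts: nobody should be able to see the next assignment, and nobody should be able to work it out. Envelopes deal with the first. A fixed and known block size weakens the second, because once one arm has used its five places, every remaining place in that block belongs to the other arm.

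That deduction needs sight of earlier assignments, which is plausible here. One arm receives a home programme with weekly calls, and the other continues the clinics' usual rehabilitation. A person who knows the next arm and applies a judgment-based exclusion could, knowingly or not, let that knowledge affect who enters. What would be at stake is the comparability of the arms at baseline, for example in frailty or mobility, and with it the comparisons of function, gait and quality of life. Assessor blinding and intention-to-treat analysis do not repair selection that happens before randomisation.

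**Working it through.** The documents give no figure for predictability, so there is none to reproduce.

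**Inputs.** Block of 10, split 5+5 (5.8). Separate lists by HIV status (5.8). 36 per group, four groups and 144 per site (5.6), hence 2 × 36 = 72 per HIV stratum per site. Assumptions not in the documents: which earlier allocations the recruiter sees, whether block starts are known, and whether each site has its own list.

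**1. Full visibility, one list per site and stratum.** There are C(10,5) = 252 equally likely blocks. A place is certain when one arm has already used its 5 places. After i earlier places, the probability is 2 × C(i,5)/252:

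| Place in block | Probability that it is certain |
|---|---|
| 1 to 5 | 0 |
| 6 | 2 × 1/252 = 0.8% |
| 7 | 2 × 6/252 = 4.8% |
| 8 | 2 × 21/252 = 16.7% |
| 9 | 2 × 56/252 = 44.4% |
| 10 | 2 × 126/252 = 100% |

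The sum is 1.67 per block, which agrees with the closed form 2 × 5/(5 + 1) = 10/6. The share is 1/6 = 16.7%.

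A stratum of 72 holds 7 full blocks and 2 further patients, so 7 × 1.667 = 11.7 certain allocations (16.2% of 72). Per site this is 2 × 11.7 = 23.3 of 144.

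**2. Partial visibility.** Suppose hospitals share a list and staff see each earlier allocation with probability p, while still knowing the block starts. Certainty requires having seen all five of one arm, so the share becomes p⁵/6:

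| p | Certain share |
|---|---|
| 1 | 16.7% |
| 0.8 | 5.5% |
| 0.7 | 2.8% |
| 0.5 | 0.5% |
| 1/3 | 0.07% |

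**3. Best guess.** Always guessing the arm with more places left is right in [5 + (2¹⁰/252 − 1)/2]/10 = (5 + 1.53)/10 = 65.3% of allocations, against 50% by chance.

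**4. Varying block sizes.** Simulation of lists of 72, with an observer who sees every allocation and knows the set of sizes but not their order:

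| Scheme | Certain, of 72 | Best guess right |
|---|---|---|
| Fixed 10 | about 11.5 to 11.8 (16%) | about 65% |
| Random 6, 8, 10, 12 | about 0.6 to 0.7 (about 1%) | about 65% |

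**The case against.** A reader might infer that clinic staff will know one in six allocations and that the functional comparisons are therefore biased. The documents do not support that.

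- **Who sees what.** Nowhere is it stated that recruiters deliver treatment, make the weekly calls or see a tally of assignments. That they can see the arms is inferred from the nature of the interventions and from who is listed as blinded.
- **Which list.** Section 5.8 stratifies by HIV status only. Section 5.3 names three hospitals, and the Nigerian site is itself two of them. A list shared between hospitals would bring the certain share far below one in six. The per-site target of 144 makes separate lists plausible but does not establish them.
- **Existing safeguards.** Allocation is independent, sampling is consecutive, recruitment is tied to routine follow-up visits, and eligibility is assessed before allocation. These leave less room to skip or delay a patient, and baseline measurements would show a gross imbalance.
- **Size of the gain.** Ten is already a fairly large block. Varying the size hardly changes best-guess prediction, and selection can act on a good guess as well as on certainty.

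All four stand as limits on the size of the point, but none removes it. Independent allocation and envelopes do not prevent deduction from earlier visible assignments and a known block size, and the exclusion for severe illness remains a matter of judgment. Envelope numbering and sealing are operational details that an article may leave out, so they are no part of this point.

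**Conclusion.** The point holds as a design weakness that is cheap to remove; it is neither an error nor a contradiction in the plan. Fixing and publishing one block size of 10 allows up to one in six allocations, about 12 of 72 per HIV stratum per site, to be deduced with certainty. That ceiling rests on three assumptions: recruiters see every earlier allocation in the stratum, they know where blocks begin, and the list is confined to their site. With half of a shared list visible it is about 0.5%. A route to selection at enrolment is therefore possible, but no bias is shown and none can be quantified from the documents. The matter is minor and does not call the trial's validity into question.

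**What to change.** In section 5.8, replace the single block size with a statement that the independent research support generates each list with randomly varying block sizes (for example 6, 8, 10 and 12) and that these are not disclosed to recruiting staff until recruitment closes. It would help to add whether lists are separate for each hospital, since the size of the problem depends on it.

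The cost is a new list and one protocol sentence; sample size, visits and analysis are unchanged. The largest possible imbalance in an unfinished block rises from 5 to 6, half of a block of 12. The benefit is the near removal of certain foreknowledge, not of guessing.

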### Participant

5.6

*Sampling and sample size:* Consecutive sampling will be used to recruit the participants. Using the statistical superiority sample size design,^[34]^ a sample of size of 36 participants per group will be sufficient to show a statistical difference in the bone mineral density between the control and the experimental group. For this study, the groups are divided into four which are the experimental group (HIV+ and HIV−) and the control group (HIV+ and HIV−), therefore, at least a total of 144 patients per study site will be recruited to participate in the study. The sample size will be calculated using Equation 1:(1)$$N=2\times \left\{Z_{1-\alpha /2}+Z_{1-\beta }/d2\right\}\times Pooled\;SD$$

where N = total sample size per group, *Z*_1−α/2_ = 1.96, *Z*_1−β_ = 0.845, *d*^2^ = 0.1 and pooled standard deviation = 0.093.

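### Allocation lists are defined by HIV status only, with separate site lists not stated, and the named arm comparison uses neither HIV status nor site

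*Protocol article*

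**What the plan says.** - **Design.** Section 5.2 describes a "multi-center parallel group assessor-blinded randomized controlled trial with allocation ratio of 1:1". Section 5.3 names Site 1 (one hospital in Johannesburg) and Site 2 (two hospitals in Enugu). The first hypothesis in section 3 covers both countries.
- **Size.** Section 5.6 sets 36 per group and forms four groups from arm and HIV status, so that "at least a total of 144 patients per study site will be recruited". Recruitment is consecutive, with no quota by HIV status stated.
- **Allocation.** Section 5.8 randomises "in blocks (10 numbers equally distributed into intervention and control groups"). It continues "There will be two blocks namely" and lists only HIV-positive and HIV-negative. Neither site, hospital nor country appears. Concealment is by opaque envelopes.
- **Comparator.** The control arm in section 5.4 is the "usual rehabilitation programme as conducted by the various clinics".
- **Analysis.** Section 5.15 compares continuous outcomes between groups with an independent t-test or a Mann–Whitney test. It mentions neither HIV status nor site.

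**The concern.** The sample size is stated by site and by HIV status, but the allocation strata are stated by HIV status alone. If sites draw on a common list, equal arms within each site are left to chance.

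Site could matter here because usual care is clinic-specific. The Discussion also expects contextual and racial differences to influence the effect of exercise on BMD. In a pooled comparison, a chance difference in the country mix of the arms adds noise to the estimated effect, and the stated test does not remove it. The test also makes no use of HIV status, the one factor on which allocation is stratified.

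What is at stake is precision and chance balance. The validity of the randomisation is not in question.

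**Working it through.** **The plan's own figures.** 4 groups × 36 = 144 per site, which reproduces. The 36 itself does not follow from section 5.6. Reading the effect as a difference of 0.1 with SD 0.093, the standard formula gives 2 × (2.805 × 0.093 / 0.1)² = 13.6, so 14 per group; Equation 1 as printed gives about 1.9. That is a separate matter. Here 36 is taken as the protocol's target.

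**Inputs.** Blocks of 10, 5:5 (5.8). Target of 36 per arm in each site and HIV stratum, so 72 per site and stratum (5.6). Two sites of equal size (assumption). Z values 1.96 and 0.845 (5.6).

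**Reading A: one HIV list of 144, drawn in mixed order by both sites.** In 20,000 simulated lists the intervention count at one site had mean 36, SD 3.04 and 95% range 30 to 42. It was off by 5 or more in 14% of runs, and the smaller arm had 32 or fewer in about 24%. A closed-form check, treating the site's patients as a random 72 of 144 with 72 in each arm, gives √(72 × ½ × ½ × 72/143) = 3.01.

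**Reading B: the same list, cut in order after 72.** In 50,000 simulated lists the first site always had 35 to 37 in the intervention arm. The second had 33 to 39 at the extremes (SD 1.06) and was off by 3 or more in about 1% of runs.

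**Reading C: a separate list per site and HIV stratum.** Each arm has 35 to 37, and the split is exactly 36/36 in about 56% of runs, because 72 is not a multiple of 10.

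**Power effect of unequal arms (per-site comparison).** With 36/36 the difference detectable at 80% power is 2.805 × √(2/36) = 0.661 SD. Power for that difference is Φ(0.661 / √(1/n₁ + 1/n₂) − 1.96):

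| Split | Power |
|---|---|
| 36/36 | 80.1% |
| 30/42 | 79.0% |
| 28/44 | 78.1% |

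**Precision effect of site (pooled comparison, reading A).** Assume the sites differ by 0.5 SD in the outcome; the article gives no figure.

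- Variance: with equal sites, ignoring site multiplies the outcome variance by 1 + 0.5²/4 = 1.0625, about 6%.
- The same effect as a shift in one stratum's arm difference: SD = 0.5 × 2 × 3.04/72 = 0.042, so a 95% range of about ±0.08 SD. The difference detectable with 72 per arm is 2.805 × √(2/72) = 0.47 SD, so ±0.08 is some 18% of it.
- These are one quantity seen twice: 0.042² ≈ 0.0018 and (2/72) × 0.0625 ≈ 0.0017. They must not be added.

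**HIV status.** Allocation balances HIV status. A two-sample test pooled over HIV status still leaves any HIV difference in its error term, so the gain from stratifying is not used.

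**The case against.** The strongest reply is that two block series within each site is a natural reading. Section 5.6 forms its four groups per site, and two HIV series times two arms gives exactly those four. Section 5.12 introduces the recruitment and allocation process for the Johannesburg hospital alone. Opaque envelopes cannot easily be drawn in mixed order from Johannesburg and Enugu, and no central randomisation is described. If a list were simply divided in order, little would need repair. A condensed article may also leave list preparation and model covariates to fuller documents.

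Much of this stands. The article does not state a list shared across countries, and reading A is the least workable with envelopes. It does not state separate lists either: it counts two series, not four, and even a list per country would leave the two Enugu hospitals undefined. The scope argument is weaker for the analysis, because section 5.15 names its tests and those tests omit the factor that section 5.8 stratifies on.

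A reader might go further and infer that country confounds the arm comparison. The documents do not support that. Allocation is random, so any imbalance is chance, and the unadjusted t-test already carries between-site variation in its standard error, so type I error is not inflated. The two harms also do not occur together: in a per-site analysis country cannot differ between arms, and in a pooled analysis 36 per site is not the relevant target.

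**Conclusion.** The point holds in a limited form. The article fixes its strata by HIV status alone for a trial sized per site with clinic-specific usual care, does not say that lists are separate by site, and names a test that uses neither factor.

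The size depends on how the lists are used: about 30 to 42 around 36 under mixed drawing, and about 1 to 3 off under a consecutive cut. Unequal arms cost about 1 point of power. Ignoring site costs about 6% in variance, on the assumed 0.5 SD site difference with two equal sites. This is imprecision and not bias.

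It would also be wrong to infer that site lists alone would secure 36 per group. Consecutive sampling without an HIV quota leaves the number in each HIV stratum open. The change is still worth making, because it is specific, nearly free and better than the stated method.

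**What to change.** - **Section 5.8:** state that a separate blocked list is generated for each site-by-HIV stratum, and define site as country (four lists) or as hospital (six, if the two Enugu hospitals recruit separately). This must be settled before the first allocation.
- **Section 5.15:** analyse continuous outcomes with a model that includes arm and HIV status and, in any analysis that pools sites, site.

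The cost is the extra envelope sets and one line of analysis text. The change balances arms within each stratum to within about one patient at 72 per stratum. It does not by itself deliver 72 HIV-positive and 72 HIV-negative patients per site, so the article should also say how that split will be reached or that it is not guaranteed.

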### Blinding

5.9

The assessors and the data analysts will be blinded to the participant's assigned groups.

### Assessments

5.10

Baseline and follow up assessment will be conducted by a qualified physiotherapist (Research assistant) who will be blinded to the study.

### Procedure

5.11

#### Pilot study

5.11.1

A pilot randomized controlled trials will be conducted to evaluate the feasibility of the study procedure and prepare for unforeseen logistical circumstances. The recruitment process, randomization, intervention protocol, and assessment using the outcome measures exactly as proposed will be tested. A sample of eight participants per group, which is ∼10% of the estimated sample size will be recruited for the pilot trial. After recruitment, baseline (2-weeks post-surgery) assessment of the variables will be measured, followed by a 6-week (post-surgery). The control group will continue with their usual treatment programme. Participants in the experimental and control groups will be re-assessed at the end of the 4-week intervention programme. If there were no changes to the study procedure, the pilot participants would be included in the main study. If there are amendments to the protocol, the changes will be communicated to the relevant bodies.

### Main study

5.12

The research will recruit patients with femoral fracture being managed at the orthopaedic department at CHBAH, and the following process will be used as a guide for the recruitment, blinding, and allocation. The main study procedure will follow the recruitment, allocation, blinding and intervention guidelines as presented. The CONSORT diagram below in Figure 1 will be used to report the recruitment and allocation of the participants. The time of recruitment and assessment is the usual routine clinic check-up of the patients in the orthopaedic surgery department (2-weeks, 6-weeks, 12-weeks, and 6-months post-surgery).

### Reporting serious adverse events

5.14

Reports of health deterioration warranting hospitalization or resulting in the death of any participant will be reported to the PI within 24 h. All participants must be informed of such developments within 72 h and be required to re-consent to continue with the trials.

### Statistical analysis

5.15

Data to be collected shall include discrete and normally distributed continuous variables. The normal distribution of the continuous variables will be tested using the Shapiro–Wilk test, and depending on the outcome, parametric or non-parametric statistics will be used to analyze the data. The change in the categorical outcomes across the time points will be measured using the McNemar's test. The difference in the continuous outcomes between the groups will be measured using the independent *T*-test (parametric) and Mann–Whitney *U* test (non-parametric). Intention to treat analysis method will be used for this study. Alpha shall be set at *P* < .05 (two-tailed). All analyses will be intent-to-treat and missing data will be treated as missing.

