**Methods and design::**

The study is an assessor-blinded randomized controlled trial. Patients managed with internal and external fixation for femoral shaft fracture at the study sites will be recruited to participate in the study. The participants will be recruited 2 weeks post-discharge at the follow-up clinic with the orthopaedic surgeon. The study population will consist of all persons with femoral fracture and HIV-positive and negative (HIV-positive medically confirmed) aged 18 to 60 years attending the above-named health facilities. For the HIV-positive participants, a documented positive HIV result, as well as a history of being followed-up at the HIV treatment and care center. A developed home based exercise programme will be implemented in the experimental group while the control group continues with the usual rehabilitation programme. The primary outcome measures will be function, gait, bone mineral density, physical activity, and QoL.

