## Research significance

4

The proposed trial will compare the effect of a home-based physical exercise-training programme in the management of femoral fracture to the usual physiotherapy management programmes with specific outcomes of BMD function and inflammatory markers.

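### Categorical outcomes are given only McNemar's test, which compares visits within patients, so as written none is compared between exercise and usual care

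*Protocol article*

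**What the plan says.** Section 5.15 (Statistical analysis) is the only place in the protocol article that names statistical tests. It expects more than one type of data: "Data to be collected shall include discrete and normally distributed continuous variables". It then assigns tests by type.

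- Categorical outcomes: "The change in the categorical outcomes across the time points will be measured using the McNemar's test".
- Continuous outcomes: "The difference in the continuous outcomes between the groups will be measured using the independent" t-test, or the Mann–Whitney U test if normality fails.

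The design under Phase two (5.2) is a "multi-center parallel group assessor-blinded randomized controlled trial with allocation ratio of 1:1". Research significance (section 4) states the question: "The proposed trial will compare the effect of a home-based physical exercise-training programme in the management of femoral fracture to the usual physiotherapy management programmes". Main study (5.12) sets four assessments: "2-weeks, 6-weeks, 12-weeks, and 6-months post-surgery". The abstract gives the primary outcomes: "The primary outcome measures will be function, gait, bone mineral density, physical activity, and QoL". None of them is declared categorical.

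**The concern.** The trial randomises patients in order to compare two programmes. For categorical outcomes the test that is named compares each patient with himself or herself at another visit. A significant result says that patients changed. It does not say that exercise changed them more than usual rehabilitation did.

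This matters in a fracture population, where improvement over six months is plausible in both arms. If an analysis plan copies this sentence, the trial could report P values for its categorical outcomes that reflect recovery, with no estimate of the programme's effect and no confidence interval for it.

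**Working it through.** **1. Text check.** The two sentences of section 5.15, side by side:

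| Outcome type | Comparison described | Test | Compares arms? |
|---|---|---|---|
| Categorical | change across time points | McNemar | no |
| Continuous | difference between groups | t-test / Mann–Whitney U | yes |

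No chi-square, Fisher, logistic, ordinal or GEE comparison of arms appears anywhere in the article. The sentence that does compare groups is expressly limited to continuous outcomes.

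**2. What McNemar's test uses.** For a binary outcome at two visits, let b be the number who improve and c the number who worsen. The exact two-sided P value is 2 × P(X ≤ min(b, c)) with X ~ Binomial(b + c, 0.5), capped at 1. Arm does not enter. The test gives the same answer whether the other arm did better, worse or equally well.

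Example: b = 11 and c = 2 gives P = 2 × (1 + 13 + 78)/8192 = 184/8192 = 0.022. If both arms show exactly 11 and 2, both are significant and the arms do not differ in change at all.

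**3. Fit to the schedule.** The test takes one pair of binary measurements. There are four assessments, and section 5.15 does not name the pair.

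**4. How often recovery alone gives significance.** The protocol states no figure on this, so there is none to reproduce. Inputs from the document: two-sided alpha 0.05 (section 5.15) and 36 per group (section 5.6). There the groups are experimental and control, each split by HIV status, with 144 patients per site. So 36 is one arm-by-HIV cell at one site, 2 × 36 = 72 is one arm at one site, and 2 × 72 = 144 is one arm over both sites.

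Assumed, not in the document: the proportion improving (u) and worsening (d), identical in both arms.

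Probability of significance = Σ over m of P(M = m) × P(exact P < 0.05 given m), where M ~ Binomial(n, u + d) is the number of discordant pairs and, given m, the number improving is Binomial(m, u/(u + d)). By exact enumeration:

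| Improve / worsen (assumed) | n = 36 | n = 72 |
|---|---|---|
| 30% / 5% | 68% | 96% |
| 25% / 5% | 51% | 87% |
| 20% / 10% | 12% | 27% |
| 15% / 10% | 4% | 9% |

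In every row the true difference between arms is zero. The first row is a strong-recovery case and the last a weak one, so the rate depends heavily on the assumption.

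**5. Contrast with a between-arm test.** A simulation (100,000 runs per scenario) used an assumed 50% baseline proportion, 20% to 40% improving and 8% to 10% worsening, identical in both arms. A two-proportion test between arms at follow-up rejected in 4.9% to 5.3% of runs. A between-arm test keeps its 5% level under recovery.

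**The case against.** **No affected outcome is named.** This stands, and it limits the weight of the point. Section 5.15 speaks of categorical outcomes without listing any. The sample size rests on bone mineral density, and the hypotheses concern strength, gait speed, bone density, function, body composition and CD4 count. These are essentially continuous and do have a between-arm test. A reader might infer that EQ-5D levels or IPAQ-SF activity classes, and with them two primary outcomes (quality of life and physical activity), go untested. The article does not say that either instrument will be analysed by category.

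**The full protocol or analysis plan may supply the comparison.** That is possible, and an article's silence would be no finding. But the article is not silent. It names a test for these outcomes, that test is of the wrong kind for the randomised question, and the between-group tests are reserved for the other outcome type.

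**A paired test is natural for change over time.** True. The sentence does not say that McNemar's test will be run separately by arm or that efficacy will be claimed from it. A reader might infer that significance in one arm and not in the other will be presented as a treatment effect. That would be invalid, but the document does not propose it.

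**The temptation to say that half of null trials would mislead.** With p the chance of significance in one group, exactly one of two groups is significant with probability 2p(1 − p). At 25%/5% and n = 36, p = 0.506 and this is 2 × 0.506 × 0.494 = 50%. But 36 is one HIV stratum's arm at one site, not a trial arm. At the same rates the figure is 22% with 72 per arm and 0.9% with 144 per arm. It does not always fall: at 20%/10% it rises from 21% at 36 to 39% at 72. No single figure for the trial is supported.

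**Four visits do not rule the test out.** Correct. It can be applied to baseline against one chosen visit. The fault is that no visit is chosen.

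**Conclusion.** The point holds and should be fixed. It does not undermine the trial's main comparison of bone mineral density. As section 5.15 stands, categorical outcomes receive a within-patient test only, and the randomised comparison is not made for them. This follows from the text and depends on no assumption.

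The practical size cannot be fixed from the document. It depends on which outcomes are categorical, which is not stated, and it may be confined to secondary or categorised outcomes. The illustration that recovery alone produces significance (68% of groups of 36 and 96% of groups of 72 at 30% improving and 5% worsening) rests on assumed rates. Across the assumptions shown, the figure for groups of 36 runs from 4% to 68%.

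**What to change.** In section 5.15:

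- List the outcomes that will be analysed as categorical.
- For each, state a between-arm comparison at a named visit. Logistic regression for a binary outcome or proportional-odds regression for an ordinal one would serve, adjusted for the baseline category, HIV stratum (the two allocation blocks in section 5.8) and site, and reported as an odds ratio with 95% CI. A chi-square or Fisher test would do where counts are sparse.
- Keep McNemar's test, if wanted, as a description of change within each arm, with the pair of visits named and a statement that it is not used to judge the programme's effect.

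A longitudinal mixed model or GEE is an option but is not needed to close the gap. The cost is analysis wording only: no new data and no change to visits or sample size. The change should be made before unblinding.
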